### Data safety

The confidentiality of research participants is secured by providing unique study identifiers unrelated to the real name.

The Coordination Centre for Clinical Trials (KKS) in Heidelberg is involved in preparing the investigator site file. Due to the online-based nature of the intervention, classical site visits are not necessary. Instead, pre-trial visits in terms of profound explanation of online content and all aspects related to delivery of the intervention took place. In addition, an independent data safety and monitoring board (DSMB) was established to monitor the collection and analyses of data.

Computerized assessments guarantee the highest level of data integrity and quality, i.e. missing data will be minimized and false data entry will be prevented. Online access allows for continuous monitoring of data collection, documentation of access logs, and traceability of all entered data (user and timestamp) as well as restoration of all previous states. A Distributed Replicated Block Device (DRBD)-based cluster will provide synchronous replication of all data during data entry on two separate servers and highest availability. In addition, full and incremental backups will be conducted following a predefined back-up plan. Data storage and transfer will be encrypted. Access to the data will be strictly limited to authorized persons and will be password-protected. All servers are located at the University Hospital Heidelberg.

### Harms

In view of the non-invasive intervention, the risk for participants is considered marginal. Irrespective of the individual allocation to one of the treatment arms, participating adolescents and young adults benefit from receiving psychoeducation on NSSI and associated mental distress. Adolescents will be instructed on the crisis procedures mentioned above. There is no obvious risk for participants. The independent KSS Heidelberg will provide expert advice and monitoring regarding all aspects of safety. Beyond that, the DSMB will be informed about adverse events, such as suicidal acts.

### Ethical issues and dissemination

The study will be conducted in accordance to the declaration of Helsinki and the rules for physicians of the medical association (“Landesärztekammer”) of Baden-Württemberg in their currently valid version. Study participation is voluntary. Consent can be withdrawn at any time without stating the reason and without any individual disadvantage for subsequent medical care. All participants will need to consent electronically to the terms of the study. In case of study withdrawal, previously collected data will be destroyed if desired unless data are already included in analyses. A waiver for parental consent was obtained from the institutional review board of the medical faculty at the University of Heidelberg. Ethics committees are able to waive paternal informed consent if studies are expected to result in great benefits for a specific target group or if studies could not be conducted otherwise [53]. Both points apply to the present study. Beyond that, the study is a non-invasive low-risk study and within the medical community, the age of 14 is considered to be the age when minor participants are able to consent to participation in low-risk studies [54, 55]. Cognitive abilities are comparable to those in adults at the age of 14 years [56]. Furthermore, the study is about reducing obstacles in receiving professional help. Thus, asking for parental informed consent would increase hurdles, especially for adolescents who are often struggling to receive adequate professional help [57].

The study protocol has been approved by the ethics committee in Heidelberg for consulting of professional conduct before the start of our study.

In the case of relevant protocol modifications, the institutional review board of the medical faculty at the University of Heidelberg will be informed and an amendment will be submitted. Furthermore, information within the German Clinical Trials Register will be updated to inform the public about possible changes.

All confidential information is subject to medical confidentiality and to the requirements of the European, Federal and State Data Protection Act (Europäische Datenschutzgrundverordnung, EU-DSGVO, Bundesdatenschutzgesetz, BDSG and Landesdatenschutzgesetz, LDSG). The data will be stored and processed in a pseudonymized manner. No third parties will gain insights into the original data.

Beyond regular journal publication, general strategies are planned to disseminate trial results: coordination and participation in scientific meetings (scientific dissemination) as well as dissemination of materials created in the subproject STAR-TRAIN, which develops practical instructions for the contact to adolescents and young adults with NSSI in primary care practice (dissemination to the public). The use of professional writers is not intended. Access to the protocol is ensured through the registration and regular update of the trial in the German Clinical Trials Register (STAR: Self-Injury: Treatment, Assessment, Recovery - Online Intervention for Adolescent Nonsuicidal Self-Injury - A randomized controlled trial; http://www.drks.de; DRKS00014623; registration date: 22 May 2018).

## Discussion

NSSI is a significant problem in adolescents and young adults, associated with severe psychopathological distress and potential long-term consequences [4–7]. Available intervention options are limited in their outreach and often fail to reach youth in rural areas and those with low help-seeking behavior. An online intervention may help to overcome existing barriers and improve general access to care for adolescents and young adults engaging in NSSI. However, so far, no study has addressed the effectiveness of online interventions for this target group. Thus, this is the first RCT to develop and evaluate an Internet-based short-term treatment for NSSI in adolescence and young adulthood. The present study and related intervention make several advances in the treatment of NSSI and build upon previous work in innovative ways.

First, we focus on NSSI, which is a significant issue in the mentioned age group. Second, we provide an evaluated short-term program addressing NSSI specifically. Third, we use an Internet-based approach to deliver therapy content. Intervening via this medium offers a number of advantages over face-to-face interventions and promises to reach a significant number of affected individuals regardless of their place of residence. In addition, help-seeking is considerably low in the target group and online interventions may lower barriers for young people to seek help.

## Limitations

Despite the mentioned advantages, potential limitations of the study design should be acknowledged. Participant drop-out is a potential challenge, particularly given the online nature of the intervention. Based on a Cochrane Review [58], attrition rates from 4% [59] up to 21% [60] were reported within face-to-face treatments of adolescent self-harm (including NSSI). Concerning online interventions for adolescents with diagnoses of depression [61, 62] and anxiety [61, 63], drop-out rates from 6% [64] up to 31% [65] were reported. Considering the mentioned studies, an attrition rate of 30% to T1 and 50% to T2 is expected, expecting *n* = 504 adolescents to complete the intervention. The study is suitably powered even down to a completer sample of *n* = 344 adolescents.

Another potential limitation is that all participants will be able to access alternative treatments outside of the trial. Information will be collected from participants about menthal health service usage and the potential impact of this on outcomes will be statistically controlled for.

In addition, we are not able to diagnose mental disorders because of the exclusive use of surveys. This is due to the online character of the study.

The provision of an online intervention, tailored to the needs of adolescents and young adults, may provide an easily accessible, cost-effective, and flexible medium for improving mental health outcomes for affected individuals.

## Trial status

Protocol version 1.0, 25 April 2018.

The trial is scheduled to be completed by 31 October 2021. Recruitment began on 1 November 2018 and recruitment will be completed approximately by 31 October 2020.

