**Methods:**

The present project aims to develop and evaluate an online intervention for adolescents and young adults with NSSI based on the content of a recently evaluated face-to-face short-term program that includes elements of CBT and dialectical behavior therapy (DBT): “The Cutting Down Programme” (CDP). The efficacy of the new online CDP intervention will be tested in a randomized controlled trial (RCT) in which *n* = 700 youths engaging in repetitive NSSI will participate in either an online psychoeducation (*n* = 350) or online CDP (n = 350). Within a postline assessment four months after baseline (end of treatment; T1), and follow-up evaluations 12 and 18 months after baseline (follow-ups; T2 and T3), NSSI and comorbid symptoms as well as quality of life will be assessed. It is hypothesized that participants receiving online CDP report a greater reduction in the frequency of NSSI within the last three months at T2 (primary endpoint) compared to those receiving online psychoeducation. Exploratory analyses will focus on predictors of treatment outcome.

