## Methods/Design

### Setting and recruitment

The present trial is a study within the consortium “Self-injury-Treatment: Assessment, Recovery (STAR).” Cooperating study sites (Ulm, Landau, Mannheim, Karlsruhe, and Berlin) will investigate the natural course of NSSI as well as psychocological and neurobiological predictors and improve ways to dessiminate specific knowledge on NSSI to primary caregivers.

We aim to include *n* = 700 adolescents and young adults aged 15–21 years in the trial. They will be randomly assigned to either receive the online CDP or online psychoeducation only. Participants in both groups will be assessed at the beginning (baseline; T0), 4 (post-line; T1), 12, and 18 months after the initial baseline assessment (follow-up; T2, T3) in order to evaluate treatment effects. The flowchart of the trial is shown in Fig. 1. The schedule of this trial is shown in Fig. 2 (Additional file 1).

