### Procedure and randomization

Before inclusion, participants will be provided with written information on the study’s background, aims and procedures, the online CDP and online psychoeducation, randomization, the advantages and risks of participating, data collection and data safety regulations, as well as voluntary participation.

Informed consent will be obtained after an initial screening phase within T0 to check for eligibility and before registering on the study website. Participants confirm by ticking a box on the website that they have read and understood the provided information and that they are willing to participate.

Within the self-report assessment and on the study platform, participants will be informed that there is no immediate check of the data they enter and thus no immediate measures can be guaranteed in case a participant reports acute suicidality. Participants will be made aware of emergency numbers in case of acute suicidality.

After providing informed consent, participants have to provide an email address as well as a username in order to register for the study. An activation link will be sent to the email address provided. Once the address has been verified, a unique code will be generated and assigned to the participant, in order to enable the matching of follow-up assessments.

After consent and registration to the platform, all eligible participants will be asked to complete a 45-min assessment within T0. After completion of the assessment at T0, participants will be randomized to the online CDP or the online psychoeducation and will be invited to participate in assessments at T1, T2, and T3. To promote participant retention, participants will be reminded to participate in the assessments via standardized e-mails at each point in time. Within a first e-mail, participants receive an invitation as well as a link to the assessment. After 3 and 14 days, participants receive reminder e-mails for the assessment. This applies to every assessment point.

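### The stated completion date of 31 October 2021 is about six months too early for the 18-month T3 assessment planned for every participant

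*Protocol article*

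**What the plan says.** All the dates are in the Trial status section of the protocol article. On accrual it says: "Recruitment began on 1 November 2018 and recruitment will be completed approximately by 31 October 2020". On the end of the study it says: "The trial is scheduled to be completed by 31 October 2021".

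The follow-up schedule is given in several places, always in the same form. Setting and recruitment has both groups assessed at baseline, at 4 months and at "12, and 18 months after the initial baseline assessment (follow-up; T2, T3) in order to evaluate treatment effects". The Methods paragraph of the Abstract gives the same 12 and 18 months for T2 and T3. Procedure and randomization says that randomised participants "will be invited to participate in assessments at T1, T2, and T3". Data assessment has the outcome measures collected at all four time points, T3 included; only the evaluation of the online programme is confined to T1.

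Each invitation is followed up by e-mail: "After 3 and 14 days, participants receive reminder e-mails for the assessment". The article applies this to every assessment point.

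The article nowhere restricts T3 to participants who enrolled early, and nowhere defines completion in a way that leaves T3 out.

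**The concern.** The completion date equals the stated recruitment close plus 12 months. That fits T2, the primary endpoint, but not T3. On these dates the later enrollees would have no T3 because the calendar ran out, not because they stopped responding.

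T3 is the only assessment after the primary endpoint, so it carries whatever the trial can say about whether an effect lasts. A T3 gap fixed by enrolment date would come on top of ordinary attrition, which the Limitations section already expects to reach 50% by T2.

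The handling of that gap also matters. The Statistical analysis section fills missing data by carrying the last value forward, on the assumption that people who dropped out did not improve relative to baseline. It does not separate data that were never due from data that were due and not given. If that rule were applied to T3, a late enrollee who never dropped out would be given a value from 12 months or earlier as the 18-month value.

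**Working it through.** **Inputs from the protocol article**
- Recruitment from 1 November 2018 to about 31 October 2020 (Trial status): 365 + 366 = 731 enrolment days.
- Completion by 31 October 2021 (Trial status).
- T2 at 12 months and T3 at 18 months after each participant's baseline (Abstract; Setting and recruitment).
- Reminders 3 and 14 days after each invitation (Procedure and randomization).
- Planned sample of 700 (Setting and recruitment).

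**Assumption.** The accrual pattern is not stated. Uniform accrual is the base case, and a range follows.

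**Reproducing the stated date**
- Recruitment close + 12 months (T2): 31 October 2020 + 12 months = 31 October 2021. This matches the stated completion date.
- Recruitment close + 18 months (T3): 31 October 2020 + 18 months = 30 April 2022. This does not match; it is six months later.
- Adding the second reminder: 30 April 2022 + 14 days = 14 May 2022.

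**Who cannot reach T3 by the stated end**
- Latest enrolment with T3 inside the period: 31 October 2021 − 18 months = 30 April 2020.
- Enrolment days from 1 May to 31 October 2020: 31 + 30 + 31 + 31 + 30 + 31 = 184.
- Share under uniform accrual: 184 / 731 = 25.2%; 0.252 × 700 ≈ 176 participants, before attrition.
- If the 14-day T3 reminder must also fall by the end date, the first affected enrolment day is 18 April 2020: 197 / 731 = 26.9%, about 189 participants.

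**Range for the accrual pattern.** Take cumulative accrual as (t/24)^k with t in months. The share enrolled in the last 6 of 24 months is 1 − (18/24)^k.

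| k | Pattern | Share | Of 700 |
|---|---|---|---|
| 0.5 | strongly front-loaded | 13.4% | 94 |
| 0.75 | front-loaded | 19.4% | 136 |
| 1 | uniform | 25.0% | 175 |
| 1.5 | back-loaded | 35.0% | 245 |
| 2 | strongly back-loaded | 43.8% | 306 |

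The uniform row differs by one person from the day count above because it works in whole months.

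**Range for the recruitment close** (uniform accrual), since that date is only approximate:
- Close on 31 July 2020: 14.4%.
- Close on 30 September 2020: 21.9%.
- Close on 31 October 2020: 25.2%.
- Close on 30 November 2020: 28.1%.

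The share would reach zero only if recruitment closed by 30 April 2020, six months before the stated date.

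**Check on T2.** With the stated close, no T2 due date falls after 31 October 2021. Some reminders would. The 3-day reminder is late for the last 3 enrolment days (3 / 731 = 0.4%, about 3 participants), and the 14-day reminder for the last 14 (14 / 731 = 1.9%, about 13 participants).

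**The case against.** The strongest reply is that the primary hypothesis, the primary endpoint and the only model written out all concern T2, and that no hypothesis is tied to T3. Completion may simply have meant completion of the primary endpoint, since the date fits T2 to the day. That limits the weight of the point but does not remove it. The article speaks of the trial without qualification and plans T3 for everyone. If another meaning was intended, a sentence saying so is still needed.

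It is also fair that the recruitment close is approximate, that the one-quarter figure depends on assumed accrual, and that it counts people before attrition. All three stand, which is why ranges are shown. If the 50% attrition expected by T2 also held at T3, the T3 responses forgone would be nearer 0.5 × 176 = 88. As a share of those responding at T3 the loss would be unchanged, provided attrition does not depend on enrolment date.

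A reader might go further and infer that the primary endpoint is cut short. Reminders for the last T2 invitations fall after the end date, and the article's own figures leave only 0.5 × 700 − 344 = 6 completers to spare. The documents do not support this:
- Every T2 due date lies within the stated period.
- A late reminder for about 2% of participants is not a lost completer; no response rate to the second reminder is given, and nothing says that links close on that day.
- Closing recruitment two weeks earlier would remove the issue.
- The 344 refers to a completer analysis, whereas the Statistical analysis section plans to include all randomised participants with values carried forward.

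A reader might also infer bias between the arms at T3. Block randomisation in a 50/50 ratio should leave late enrollees nearly balanced between groups, so no such bias is shown. Nor does the article say that the carried-forward rule will be used at T3; that consequence is conditional.

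**Conclusion.** The point holds as a contradiction between stated dates and stated design. The completion date is about six months too early for the last T3, and participants enrolled after 30 April 2020 cannot be assessed at 18 months within the stated period. That conclusion needs no assumption about accrual beyond recruitment continuing past April 2020.

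Only the size rests on assumptions: about 25% (about 176 of 700, before attrition) under uniform accrual, 13% to 44% across the accrual patterns tried, and 14% to 28% across the closing dates tried.

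The consequence is confined to T3: fewer 18-month data, a denominator that depends on enrolment date, and a risk of carried-forward values standing in for assessments that were never due. The primary analysis at T2 is not undermined. The dates should be corrected, but the point does not call the main result into question.

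**What to change.** Reconcile the Trial status dates with the follow-up schedule, in the protocol and in the register entry, in one of two ways.

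1. **Extend data collection.** Set the end after the last participant's T3 and its 14-day reminder, about mid-May 2022 if recruitment closes around 31 October 2020. The cost is about six more months of assessments that are already automated and online.
2. **Keep 31 October 2021 and limit T3.** State that T3 is planned only for participants enrolled by 30 April 2020 (by 17 April 2020 if the 14-day reminder is also to fall inside the period). Report T3 on that denominator. Treat later enrollees as administratively censored at T3, and do not impute them as drop-outs. The cost is a restated T3 denominator and lower precision at 18 months.

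If completion was meant to refer to T2 only, say so and give the separate date on which T3 collection ends.

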## Data Availability

Not applicable.

## Abbreviations

BDSG: Bundesdatenschutzgesetz
BPD: Borderline Personality Disorder
BSL-23: Borderline Symptom List-23
CBT: Cognitive Behavioral Therapy
CDP: Cutting Down Programme
DBT-A: Dialectical Behavior Therapy for Adolescents
DRBD: Distributed Replicated Block Device
DSM-5: Diagnostic and Statistical Manual of Mental Disorders, Fifth edition
EU-DSGVO: Europäische Datenschutzgrundverordnung
ITT: Intention-to-treat
KIDSCREEN: Health-Related Quality of Life Questionnaire for Children and Young People
KKS: Coordination Centre for Clinical Trials
LDSG: Landesdatenschutzgesetz
MACT: Manual-assisted Cognitive Behavior Therapy
MBT-A: Mentalization-Based Treatment for Adolescents
NSSI: Non-suicidal self-injury
NSSV-SG: NSSI Severity Questionnaire
PHQ-A: Patient Health Questionnaire-9 for Adolescents
PSS: Paykel Suicide Scale
RCT: Randomized controlled trial
SAPAS-SF: Self-report Standardized Assessment of Personality – abbreviated scale
SDQ: Strengths and Difficulties Questionnaire
TAU: Treatment as usual
